### Objectives {7}

The first aim is to assess the efficacy of incorporating the MSI into TranS-C, compared to TranS-C alone. We hypothesize that compared to TranS-C alone, TranS-C + MSI will be associated with improvements in sleep and circadian functioning, daytime functioning, well-being, and patient memory at post-treatment, 6FU, and 12FU. The second aim is to evaluate if patient memory for treatment contents mediates the relationship between treatment condition and sleep and circadian functioning. We hypothesize that TranS-C + MSI will be associated with enhanced memory for treatment relative to TranS-C alone and enhanced memory for treatment will be associated with improvements in sleep and circadian functioning at post-treatment, 6FU, and 12FU. The third aim is to assess whether previously reported poor treatment response sub-groups will moderate the relationship between treatment condition and (a) patient memory for treatment and (b) treatment outcome, such that individuals in these sub-groups may derive a greater benefit from receiving memory support. It is hypothesized that treatment effects for those in the TranS-C + MSI condition will be larger at post-treatment for individuals who are older, have fewer years of education, poorer baseline cognitive functioning, and more severe baseline sleep disruption and sleep-related impairment. Exploratory analyses will compare treatment condition on (a) patient adherence, patient-rated treatment credibility, and patient utilization of treatment contents and (b) therapist-rated acceptability, appropriateness, and feasibility.

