#### Memory assessments

Memory will be assessed using the Patient Treatment Recall Task and the Thoughts and Application Task at mid-treatment (between sessions 4 and 5), post-treatment, 6FU, and 12FU.

The *Patient Treatment Recall Task* will be used to assess participant memory for treatment contents [3]. Participants are required to spend a minimum of 5 min on the recall task and are given up to a maximum of 10 min to recall as many distinct treatment points as possible from all the sessions that they have attended so far (cumulative recall). This task has excellent interrater reliability and, in previous studies, is associated with the amount of memory support received [3, 121]. The overall number of treatment points recalled is determined using a scoring rubric developed in a previous study [3]. The number of treatment points will be summed at each measurement points to produce a single score.

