#### Sample size {14}

For Aim 1, sample size was determined by conducting a power analysis using Optimal Design [139, 140] for person-randomized, repeated measures trials with four timepoints (pre-treatment, post-treatment, 6FU, and 12FU). Using a prior dataset comparing CT + MSI and CT-as-usual for depression [25] (R01MH108657), the effect size was calculated for midlife and older adults (≥ 50 years) by averaging the effect size for depression severity at post and 6FU. This approach yielded an effect size of* d* = 0.50. To achieve 80% power, 146 participants are needed. Adding 20% for attrition results in a sample size of 176. For Aim 2, Fritz and MacKinnon [141] provide recommendations for mediation sample size. Using data from R01MH108657 for midlife and older adults (≥ 50 years), the path from the predictor (average constructive memory support) to the mediator (recall at mid-treatment) was small to medium (*f* = 0.18) and the path from the mediator (recall at mid-treatment) to outcome (functional impairment at post-treatment) was medium (*f* = 0.23). Based on these estimates, a sample size of 148 is needed. Adding an additional 20% for attrition results in a sample of 178. The powerMediation package in R [142] was used to calculate the minimum detectable indirect effect of average constructive memory support on outcomes at 6FU and 12FU via recall at mid-treatment. With the proposed sample size of 178 needed for mediation at post-treatment, a minimum standardized indirect effect of 0.56 for outcomes at 6FU and 0.66 for outcomes at 12FU can be detected. The present study focused on powering the primary timepoint of interest, post-treatment. As treatment effects tend to decline over time, we may not be adequately powered to detect statistical significance at 6FU and 12FU. Thus, effect sizes, rather than statistical significance, will be emphasized for the follow-up timepoints. For Aim 3, a minimum detectable effect size difference was calculated via PowerUp! [143]. Estimates from pre-treatment to post-treatment impairment were generated from two prior datasets: (1) midlife and older adults (≥ 50 years), who were randomized to CT + MSI and CT-as-usual [25] (R01MH108657) and (2) midlife and older adults (≥ 50 years), who participated in the pilot trial of TranS-C + MSI [24]. The moderator with the smallest estimates (education from the R01MH108657 trial) was used to help ensure adequate sample size. With an alpha of 0.05, 80% power, and a sample size of 178 (calculated for Aim 2 mediation), the MDES for the moderator effect was *d* = 0.24. Considering that this effect size is comparable to the effect size yielded by similar analyses using prior data (*d* = 0.25 in the R01MH108657 trial), the sample size calculated for Aim 2 will be sufficient to power Aim 3. Together, a minimum sample size of 178 will be sufficient to power all three aims.

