#### Aim 3: Poor treatment response sub-groups as a moderator of treatment condition and sleep and circadian functioning

HLMs will be used to assess the relationship between treatment condition and outcomes at post-treatment, with the following sub-groups included as moderators: age, education, cognitive functioning,^1^ and severity of sleep disruption and sleep-related impairment. These moderators are included in the analysis to assess whether constructive memory support received in the TranS-C + MSI treatment condition results in greater treatment outcomes in any of the sub-groups.

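### The claim that 178 participants power all three aims is unsupported for Aim 3(a): the only Aim 3 calculation concerns impairment and cannot be assumed to hold for patient memory, which has no baseline score

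*Protocol article*

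**What the plan says.** Objectives {7} gives Aim 3 two dependent variables. Poor-response subgroups "will moderate the relationship between treatment condition and (a) patient memory for treatment and (b) treatment outcome". The Abstract and the Discussion describe the aim in the same two parts. The analysis section for Aim 3 is headed "Poor treatment response sub-groups as a moderator of treatment condition and sleep and circadian functioning", while its body speaks more generally of outcomes at post-treatment.

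Sample size {14} contains one calculation for Aim 3. Its source is described thus: "Estimates from pre-treatment to post-treatment impairment were generated from two prior datasets". The moderator is education, taken from the earlier depression trial because it had the smallest estimates. At alpha 0.05, 80% power and N = 178, "the MDES for the moderator effect was *d* = 0.24". The article compares this with an effect of 0.25 from similar analyses of that earlier trial and closes: "Together, a minimum sample size of 178 will be sufficient to power all three aims".

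Memory assessments states that both memory tasks are given "at mid-treatment (between sessions 4 and 5), post-treatment, 6FU, and 12FU". Table 2 agrees: neither task has a pre-treatment entry. In the Sample size section recall appears only as the Aim 2 mediator.

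**The concern.** A power statement belongs to a particular outcome. A standardised detectable effect depends on how much of that outcome's variance is explained by covariates, and for a scale measured before and after treatment the baseline value is usually the main contributor. Recall of treatment content cannot have a baseline value, because before treatment there is no content to recall. The mid-treatment score does not take its place: it is measured after randomisation and may itself be changed by the intervention. A figure derived from pre-to-post impairment therefore cannot simply be carried across to recall.

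Patient memory is the mechanism the intervention is built to engage, and Aim 3(a) asks whether the subgroups expected to need help most gain more memory. If the all-aims sentence stands, a non-significant interaction on recall can be read as a negative result from a test with 80% power, when no such power has been shown.

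**Working it through.** **Inputs from the protocol.** N = 178, alpha 0.05, 80% power and a stated detectable effect of 0.24 (Sample size {14}); 1:1 allocation (Trial design {8}); 148 participants needed for Aim 2, raised by 20% for attrition (Sample size {14}); no pre-treatment memory score (Table 2 and Memory assessments).

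**Inputs assumed here, because the article does not state them.** Two-sided test; moderator continuous and standardised; covariates (for example age, education and the cognitive screen) explaining R² = 0 to 0.30 of recall variance.

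**Formula.** For an individually randomised trial with arm fraction P = 0.5, the detectable interaction, in outcome SD per SD of the moderator, is

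MDES = (1.96 + 0.84) × √[(1 − R²) / (P(1 − P)N)] = 2.80 × 2 × √[(1 − R²)/N].

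**Step 1: the plan's own figure.**
- N = 178, R² = 0: 5.60/√178 = 5.60/13.34 = 0.42.
- R² needed to reach 0.24: 1 − (0.24/0.42)² = 1 − 0.33 = about 0.67.

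So 0.24 does not follow from the stated alpha, power and N alone; under this formula it needs covariates explaining about two thirds of the outcome variance. A one-sided test gives 0.37 at R² = 0 and still needs an R² of about 0.59. A 50/50 binary moderator, two-sided, gives 0.84 and needs about 0.92. The covariate inputs to the plan's calculation are not given, so the figure can be neither reproduced nor refuted for impairment. An R² that high would plausibly come from the outcome's own pre-treatment value.

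**Step 2: recall, without a baseline score.**

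| Number assessed | R² = 0 | R² = 0.30 |
|---|---|---|
| 178 | 5.60/√178 = 0.42 | 0.420 × √0.70 = 0.35 |
| 148 | 5.60/√148 = 0.46 | 0.460 × √0.70 = 0.39 |
| 142 | 5.60/√142 = 0.47 | 0.470 × √0.70 = 0.39 |

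Using t rather than normal quantiles raises these by no more than 0.005.

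**Step 3: which N applies.** The plan obtains 178 as 148 × 1.20 = 177.6, so 148 is the number it means to analyse. Losing 20% of 178 leaves 178 × 0.80 = 142.4. The Aim 3 figure is nevertheless computed at 178, which amounts to no loss before post-treatment. A participant lost before mid-treatment supplies no recall data at all.

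**The case against.** Sizing from a related outcome in earlier data is ordinary practice, and this protocol also does it for Aim 1 (depression severity) and Aim 2 (functional impairment). Aim 3 did not set the sample size; Aim 2 did. Memory is not a primary outcome, and the multiplicity-corrected confirmatory tests are confined to the three primary scales. All of that stands and limits the consequence. It does not supply a calculation for recall, and the article goes beyond silence by affirming sufficiency for all aims.

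Three stronger inferences are tempting and should not be drawn.

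- **That the sleep outcomes were left out of the calculation.** The Aim 3 sizing text says only impairment and names no scale. Functional impairment is the likelier meaning, because the Aim 2 text in the same paragraph uses that term and the education estimate comes from a depression trial. But the protocol also uses impairment for the PROMIS-SRI, and one of the two source datasets is described there as a pilot of TranS-C + MSI (although the Background describes the same reference as a cognitive-therapy pilot in depression). If functional impairment is meant, the Sheehan scale is a primary outcome and falls within treatment outcome as Objectives {7} words Aim 3(b). The sleep wording comes from a section heading.
- **That Aim 3(a) has a known low power.** Computing power on recall for 0.25 would borrow an impairment estimate for a different outcome, which is the very step criticised here. Memory is the direct target of the intervention, so the true interaction could be larger or smaller.
- **That 0.24 is an error.** With the covariate inputs unstated, this cannot be shown for impairment.

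**Conclusion.** The point holds for Aim 3(a). The statement that 178 powers all three aims is not supported for moderation of the effect on patient memory, because the only Aim 3 calculation is on another outcome and recall lacks the baseline score that would plausibly be needed to reach 0.24. Under the stated assumptions the detectable interaction on recall is about 0.35–0.42 SD if all 178 are assessed and about 0.39–0.47 SD with 142–148. These ranges rest on an assumed R² of 0–0.30, a continuous moderator and a two-sided test; a 50/50 binary moderator would double them.

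A reader might infer that Aim 3(a) has no power at all. It has some; how much is unknown, because the document gives no moderator effect on recall. What is missing is a calculation that covers it.

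**What to change.** In Sample size {14}:

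1. Limit the Aim 3 power statement to the impairment outcome actually used, and name the scale.
2. Remove the all-aims sentence, or qualify it so that it does not extend to Aim 3(a).
3. State the detectable interaction for post-treatment recall, computed without a baseline score and at the number expected after attrition, with the assumed covariate R², sidedness and form of the moderator.
4. If the impairment scale was not a sleep measure, also give the figure for PROMIS-SD and PROMIS-SRI, each using its own pre-post correlation.

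In the Aim 3 analysis text, commit to reporting Aim 3(a) as interaction estimates with confidence intervals, so that a null result is not taken as a negative finding from a test with 80% power. The article already takes this line for the 6- and 12-month timepoints, where it puts effect sizes ahead of significance. Formally labelling Aim 3(a) exploratory is optional.

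The cost is some rewording and one or two recalculations. Enrolment is unchanged, and the stated detectable effect becomes less favourable.

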
### Recruitment {15}

Strategies for achieving adequate participant enrollment include recruiting participants through community-based organizations serving middle-aged and older adults and from the distribution of fliers in the community (e.g., health care clinics, senior centers, libraries).

## Assignment of interventions: allocations

### Sequence generation {16a}

Simple randomization will be used to allocate participants to one of the two treatment arms with a 1:1 allocation ratio. Randomization will be conducted using a computerized, random-number generator in Excel. The resulting random number sequence will be used to assign each subsequent participant to a treatment condition. Randomization is stratified by age (50–69, ≥ 70), as there is evidence that these variables can impact sleep and/or treatment outcomes [60, 144]. The planned stratified randomization is part of the generation of the randomization sequence. We did not stratify by sex as there are no known sex differences in response to either TranS-C or the MSI.

### Concealment mechanism {16b}

Allocation concealment will be ensured as the random number sequence will not be visible to the research team prior to the participant being assigned to a treatment condition.

### Implementations {16c}

The random number sequence will be generated by one project coordinator. Other project coordinators will be responsible for enrolling participants and assigning them to treatment condition.

## Assignment of interventions: blinding

### Who will be blinded {17a}

Therapists delivering TranS-C alone will be blind to the existence of TranS-C + MSI condition. Therapists delivering TranS-C + MSI will be aware of the TranS-C alone condition to prevent them from inadvertently unmasking other team members. Patients will not be aware of their condition assignment. Only the project coordinator involved in the randomization process will know the treatment allocation of each participant. All other team members will be masked to treatment condition, including those conducting assessments, those coding treatment sessions, and biostatisticians.

### Procedure for unblinding if needed {17b}

Unblinding is not expected in the current trial, as both versions of the intervention involve minimal risk and the provider and patient are both privy to the specific treatment modules that have been delivered, emergency unblinding is not applicable.

## Data collection and management

### Plans for assessment and collection of outcomes {18a}

Potential participants will be invited to schedule a full eligibility screening assessment virtually (i.e., via phone or HIPAA-compliant Zoom). After obtaining verbal consent, inclusion and exclusion criteria will be assessed. Participants who screen positive for OSA will be required to follow additional steps to meet eligibility, participants who screen positive for OSA with no prior diagnosis will undergo home sleep apnea testing using WatchPAT® ONE (described in more detail above). Eligible participants will be invited to participate in the pre-treatment assessment. Written informed consent will be obtained prior to starting the pre-treatment assessment via HIPAA-compliant DocuSign or paper consent forms. The pre-treatment assessment, as well as all other assessments, will be conducted virtually over the phone or HIPAA-compliant Zoom. Assessments will be conducted by carefully trained and supervised assessors (i.e., UCB research staff), who enter data into HIPAA-compliant Qualtrics for all assessments. Immediately after the pre-treatment assessment, participants will complete sleep diaries for a 7-day period while wearing an actigraph. Sleep diaries will be completed by participants after receiving a daily scheduled text or email with a link to Qualtrics or collected by an assessor via daily phone calls, who enters the data into Qualtrics.

### Plans to promote participant retention and complete follow-up {18b}

Patient retention will be maximized via collaborative efforts between the therapists and assessment team. Considerable efforts will be made by the facilitators and assessors to answer questions and troubleshoot challenges (e.g., scheduling difficulties) to prevent attrition. All participants including those who discontinue treatment will be contacted and asked to complete post-treatment and follow-up assessments.

### Confidentiality {27}

All participant-identifiable data will be saved by the assessment team on a secure password-protected and HIPAA-compliant website. Participants and therapists are assigned identification numbers used to link anonymized data that is collected via HIPAA-compliant Qualtrics. When collecting assessments, assessors talk to participants on HIPAA-compliant Zoom or by phone and enter the data into HIPAA-compliant Qualtrics. Participant-identifiable data is not shared with outside entities during or after the trial.

### Plans for collection, laboratory evaluation, and storage of biological specimens for genetic or molecular analysis in this trial/future use {33}

Not applicable to the current trial as no biological specimens will be collected.

## Statistical methods

An alpha = 0.05 will be used for each primary hypothesis. The Benjamini–Hochberg procedure [145] will be used to correct for multiple testing for confirmatory analyses on the primary outcomes (i.e., PROMIS-SD, SDS, SWLS).

### Statistical methods for primary and secondary outcomes {20a}

#### Aim 1: Efficacy of TranS-C + MSI compared to TranS-C alone

Hierarchical Linear Modeling (HLM) [146–148] will be used to test for differences in the trajectories of primary and secondary outcomes across time between the two treatment groups (TranS-C + MSI vs. TranS-C alone). All primary and secondary outcomes are continuous variables (see Table 1) and will be analyzed using the same approach. The 1st level will represent within-person variation and will include dummy-coded time indicators as the predictor (0 = pre-treatment, 1 = post-treatment, 2 = 6FU, 3 = 12FU). The 2nd level will represent between-person variation and will include dummy-coded treatment condition (0 = TranS-C alone, 1 = TranS-C + MSI) and treatment-by-time interaction terms as the predictor. Interactions between treatment condition and the time indicators will be retained only if found significant at the 5% level. A significant interaction between treatment condition and time indicators would suggest that there are different trajectories across time between the two treatment conditions and will be graphed to interpret the interaction. Significant interactions will be interpreted with planned contrasts to assess if treatment effects change over time.

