### Participant measures

Across participant measures, the post-treatment time point is of primary interest.

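### Aim 1 drops the treatment-by-time terms unless they are significant; what is left averages the treatment effect over the pre-randomisation wave and contains no post-treatment contrast

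*Protocol article*

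**What the plan says.** The Aim 1 section sets out a hierarchical linear model to "test for differences in the trajectories of primary and secondary outcomes across time between the two treatment groups". Its first level "will include dummy-coded time indicators as the predictor", coded from pre-treatment (0) through post-treatment and 6FU to 12FU (3). Treatment condition and its interactions with time enter at the second level. The selection rule follows: "Interactions between treatment condition and the time indicators will be retained only if found significant at the 5% level". If the interaction is significant, "Significant interactions will be interpreted with planned contrasts to assess if treatment effects change over time".

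Three other places bear on this:

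- Participant measures: "Across participant measures, the post-treatment time point is of primary interest". Sample size {14} likewise says that the study was powered for post-treatment, and that effect sizes will be stressed at the follow-ups.
- Statistical methods: "An alpha = 0.05 will be used for each primary hypothesis", and the Benjamini-Hochberg procedure "will be used to correct for multiple testing for confirmatory analyses on the primary outcomes" (PROMIS-SD, SDS, SWLS). The p-value to be entered for each outcome is not named.
- Plans for assessment and collection of outcomes {18a}: participants are randomised after the pre-treatment assessment is complete.

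**The concern.** Because pre-treatment is an outcome wave that precedes randomisation, the true arm difference there is zero by design. Any benefit of the MSI must therefore appear as a difference between arms that is absent at pre-treatment and present later, which is a treatment-by-time interaction. The rule treats that interaction as an optional refinement to be removed when it misses 5%.

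Two things are at stake for the three primary outcomes. First, once the terms are removed, the model holds a single arm difference common to all four waves. That is not the effect at any time point, and it cannot supply the post-treatment result or the separate follow-up effect sizes that the protocol promises. Second, the data choose which model is reported. One primary outcome could enter Benjamini-Hochberg with an interaction test and another with a four-wave main effect.

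**Working it through.** **Inputs.** From Sample size {14}: d = 0.50 (obtained by "averaging the effect size for depression severity at post and 6FU"), 80% power and 146 evaluable participants; with 1:1 allocation, 73 per arm. From Statistical methods: alpha 0.05. Assumed, because the document does not give them: two-sided tests, complete data, normal outcomes with SD 1, equal correlation rho between waves (0.3, 0.5, 0.7) and no therapist clustering.

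**The plan's own figure.** The 146 can be neither confirmed nor refuted. The two-sample formula gives 126. A four-wave linear-trend formula with both variance components set to 1 gives 153, and 146 would need a reliability of about 0.87 to 0.88. The variance components are not stated. The 146 serves here only to fix 73 per arm.

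**Step 1: what the fallback coefficient estimates.** With balanced data and a random intercept it is the mean of the four wave-specific differences.

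| True effect at pre, post, 6FU, 12FU | Fallback estimate |
|---|---|
| 0, 0.50, 0.50, 0.50 | 1.50/4 = 0.375 |
| 0, 0.50, 0.25, 0 | 0.75/4 = 0.1875 |
| 0, 0.50, 0, 0 | 0.50/4 = 0.125 |

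Simulation of the rule agreed, including within the trials where the terms were dropped (for the constant effect, 0.374 to 0.380).

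**Step 2: how often the terms are dropped (joint 3-df test).** The noncentrality is lambda = (n/2) × S/(1 − rho), where S is the sum of squared deviations of the four differences from their mean. For the constant effect, S = 0.375² + 3 × 0.125² = 0.1875, so lambda = 36.5 × 0.1875/(1 − rho). The reference distribution is F(3, 432).

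| rho | lambda | P(dropped), formula | P(dropped), simulated |
|---|---|---|---|
| 0.3 | 9.78 | 25% | 25% |
| 0.5 | 13.69 | 11% | 12% |
| 0.7 | 22.81 | 1.3% | 1.5% |

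For the fading effect S = 0.1719, and the formula gives 30%, 15% and 2%. Selection also acts the other way. When the terms are kept, the post-treatment estimate under a constant 0.50 averages 0.56 at rho 0.3 and 0.53 at rho 0.5.

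**Step 3: type I error per outcome.** In this balanced setting the joint interaction test and the main-effect test are independent under the null, so counting either gives 1 − 0.95² = 9.75%. Simulated results (20,000 null trials per scenario, 73 and 89 per arm):

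| What counts as a positive result | Type I error |
|---|---|
| Joint interaction test only; no claim from the main effect | 5% |
| Joint test followed by a significant post contrast; otherwise main effect | 6.3–6.9% |
| Joint test followed by any significant contrast; otherwise main effect | 8.5–9.1% |
| Joint test; otherwise main effect | 9.5–10.2% |
| Any of the three terms singly; otherwise main effect | 16.3–17.5% |

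In the last row, 12 to 13 points come from testing three terms without adjustment, before any fallback.

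**Step 4: does Benjamini-Hochberg repair it?** No. Over three independent null outcomes at rho 0.5, the chance of any false claim is 9.2% under the fourth row and 17.6% under the fifth. It is 5.1% if one fixed post-treatment contrast is entered per outcome.

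**The case against.** The strongest reply is that the inflation is not a fixed property of the plan. The Aim 1 section describes inference only from a significant interaction and never says that a fallback main effect would count as efficacy. If the joint interaction is the sole efficacy test, the error is 5%. This stands: a reader might infer that the type I error simply is 10–17%, but the text supports that only under particular counting rules. The top of the range is also mainly multiplicity over three terms, and whether testing is joint or term by term is a detail that an unseen analysis plan may settle.

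A reader might also infer that the post-treatment contrast is never tested. That is too strong. With pre-treatment as the reference level, the treatment-by-post-treatment coefficient is that contrast whenever it is kept, and planned contrasts follow a significant interaction. It is lost when the terms are dropped.

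Dropping is a minority event at the planned effect, and rare at rho 0.7. Nor is the four-wave average always a weak test: for a constant 0.50 effect at rho 0.3, its simulated power is 90%, against 73% for the post contrast. But it still estimates 0.375, and for the fading effect its power falls to between 25% and 36%. Sample size {14} itself expects effects to decline over time.

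Finally, leaving the pre-treatment mean free in each arm might be read as a further error. It is not: the resulting contrast is valid and unbiased under randomisation, only less precise.

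What the reply does not touch is the rule itself. It is stated outright, nothing else in the document overrides it, and even the 5% reading leaves the post-treatment question unanswered whenever the joint test misses.

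**Conclusion.** The retention rule is wrong as written and should be removed. When it drops the interactions, the reported effect is exactly three quarters of a constant post-baseline effect, and less if the effect fades (0.19 for 0.50/0.25/0; 0.125 for post-treatment only). No contrast is then left at the time point that the protocol calls primary. The dilution factors are arithmetic under balanced data with a random intercept. The frequency of dropping (about 25%, 12% and 1% for a constant 0.50 with 73 per arm) rests on assumed correlations of 0.3, 0.5 and 0.7 and on a joint test.

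The error rate should be stated conditionally: 5% if only the joint interaction supports a claim; about 6–9% if the fallback can support one but a significant interaction must be confirmed by a contrast; about 10% if either counts; and about 16–17% if terms are tested singly. The document does not choose among these.

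**What to change.** Replace the retention sentence with a rule to this effect: all three treatment-by-time terms stay in the model whatever their significance; the treatment-by-post-treatment contrast is the confirmatory test for each of PROMIS-SD, SDS and SWLS; those three p-values enter Benjamini-Hochberg; and the 6FU and 12FU contrasts are reported from the same model as estimates with confidence intervals.

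Under the same assumptions, this contrast has a simulated type I error of 4.7–5.3%, is unbiased at 0.50, and has power of about 72%, 85% and 97% at rho 0.3, 0.5 and 0.7 with 73 per arm.

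As an option, for precision and not as a correction, the arms can be constrained to a common pre-treatment mean. This multiplies the variance of the post-treatment contrast by (1 + rho)/2, for example 0.75 at rho = 0.5; the document gives no value for rho.

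The cost is wording only, with no added participants or data. Recruitment is stated to run through October 2026 and no interim analysis is planned. The one thing given up is the omnibus trajectory test as a headline; it becomes a secondary description.
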